*[*31*]**.* We aim to recruit 260 patients with clinical knee OA, significant knee pain and effusion-synovitis present on MRI. To recruit the patients, we will use an established strategy [32], including collaboration with general practitioners, specialist rheumatologists, orthopaedic surgeons, and advertising through local media, social media (e.g. Facebook, Twitter and University websites), contacting past knee OA trial participants, patient support groups and hospital flyers. Patients will be recruited from four sites (i.e. Hobart, Melbourne, Adelaide, and Perth) within Australia, and each site aims to recruit 65 participants. Ethics approval has been obtained from the Tasmania Health and Medical Human Research Ethics Committee (H0017151), Monash University Human Research Ethics Committee (17684), Alfred Hospital Ethics Committee (427/18), and South Metropolitan Health Service Human Research Ethics Committee (RGS0000000957). Written informed consent or eConsent (through an online survey issued using Research Electronic Data Capture (REDCap)) will be obtained from all patients by a medical doctor at each site. The consent or eConsent form includes two optional permissions, (1) consent for their medical records to be made available to study researchers from the Australian Orthopaedic Association National Joint Replacement Registry (AOANJRR) for the purpose of checking on any knee joint replacement surgery following study completion and (2) consent to have blood samples stored for future testing and to share blood samples and associated data with other researchers, including researchers outside Australia.

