### Randomisation and blinding

Allocation of patients in a 1:1 ratio to either the active or placebo group will be by computer-generated random numbers using a central randomisation website hosted by the University of Tasmania. We will use block randomisation (permuted block design), using a block size of 4 (2 in each arm), stratified by study site and size of effusion-synovitis (Grade 1 or 2/3). This will be conducted by a staff member with no other involvement in the study.

The randomised controlled trial will be a double-blind one, with study patients, assessors, and MRI readers all blinded to treatment allocation. Allocation concealment and double blinding will be ensured by (1) the use of identical capsules for each group; (2) objective measures of knee structural changes being made by trained observers blinded to group allocation; and (3) subjective measures being taken by research assistants blinded to group allocation.

Emergency unblinding will be allowed in limited situations that impact on the safety of study participants. Code-break for the full randomisation schedule will be maintained by the administering institute. Participants who are unblinded will be withdrawn from treatment but will continue to be followed as per the planned follow-up schedule.

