### Statistical analysis

The primary analyses will be intention-to-treat analyses of primary and secondary outcomes. Per protocol analyses will be performed as the secondary analyses, for study participants consuming ≥80% of study medication between baseline and week 24 (allowing for 1 capsule (50 mg) per day).

Changes in pain scores and total effusion volume will be analysed using a linear mixed-effects model with treatment, month and their interaction (treatment × month) as covariates. The correlation within trial centres and the repeated measures will be addressed using the trial centre and participant identification as random intercepts. Month will be treated as a random effect to allow different treatment effects among participants over time. Change in outcome measures within each group and difference of the changes between groups from baseline to follow-up will be calculated using linear combinations of the estimated coefficients adjusted for the baseline values of the corresponding outcome measure (e.g. change in pain scores will be adjusted for baseline pain scores). We will also run a model that additionally adjusts the primary outcome for sex, analgesic medication, and depression. Missing data caused by loss to follow-up and nonresponses will be addressed by adding baseline complete variables that can explain the missingness to the regression models.

Secondary analysis for missing data will be performed using multiple imputation by chained equations, with 20 imputations performed by the treatment group using baseline complete variables and nonmissing values of the outcomes at baseline and each follow-up, assuming missing at random.

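### The primary pain model leaves out effusion-synovitis grade, one of the two factors used to stratify randomisation

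*Protocol article*

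**What the plan says.** All references are to the protocol article.

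- **Randomisation and blinding:** "Allocation of patients in a 1:1 ratio to either the active or placebo group", by permuted blocks "using a block size of 4 (2 in each arm"), "stratified by study site and size of effusion-synovitis (Grade 1 or 2/3"). Under Study design there are four sites, and "each site aims to recruit 65 participants".
- **Statistical analysis, primary model:** a "linear mixed-effects model with treatment, month and their interaction (treatment × month) as covariates". Centre clustering and repeated measures are "addressed using the trial centre and participant identification as random intercepts", month is also a random effect, and the estimates are "adjusted for the baseline values of the corresponding outcome measure".
- **Statistical analysis, additional model:** one that "additionally adjusts the primary outcome for sex, analgesic medication, and depression".

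Grade appears in the Statistical analysis section only for the pre-specified stratified analyses. The sentence on missing data lets baseline variables that explain missingness enter the models, but it names none.

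**The concern.** Stratified randomisation makes the arms alike on grade. A model that then ignores grade counts the between-grade variation as noise, although the design has already removed most of its contribution to the difference between arms. If grade is prognostic, the reported standard error overstates the true variability of the estimate. Intervals are too wide, p-values too large, and the test rejects a true null less often than 5%.

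The protocol gives reason to think grade is prognostic. Its Background cites population-based work in which more effusion-synovitis goes with larger later increases in knee pain. It also thought grade important enough to balance on. Yet the three covariates of the additional model are all variables that were not used in randomisation.

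**Working it through.** **1. Where each factor appears**

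| Factor | Randomisation | Primary pain model | Additional model |
|---|---|---|---|
| Site | stratified | random intercept | not mentioned as changed |
| Grade (1 vs 2/3) | stratified | absent | absent |
| Baseline pain | – | included | included |
| Sex, analgesics, depression | – | absent | included |

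**2. The plan's own sample size**

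Inputs from Sample size calculations: difference 10 mm, SDs 25.5 and 21.5, 90% power, alpha 0.05 (two-sided, from Statistical analysis), 10% loss.

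- Mean variance = (25.5² + 21.5²)/2 = (650.25 + 462.25)/2 = 556.25; SD = 23.585.
- n per arm = 2 × (1.960 + 1.282)² × 556.25 / 10² = 116.9, so 117 per arm and 234 in total; 234/0.9 = 260.
- SE = √(2 × 556.25/117) = 3.084; power = Φ(10/3.084 − 1.96) = Φ(1.283) = 90.0%.

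The stated 234 and 260 reproduce. The calculation is a plain two-group comparison and takes no credit for stratification.

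**3. What grade could explain**

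The protocol expects about 145 of 260 participants in Grade 2/3, so p = 145/260 = 0.558 and p(1 − p) = 0.2467. It gives no difference in pain change between grades; the gaps below are assumed.

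- R² = 0.2467 × gap² / 556.25
- SE inflation from omitting grade = 1/√(1 − R²) − 1
- SE with grade = 3.084 × √(1 − R²)
- Power with grade = Φ(10/SE − 1.96)

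| Gap, Grade 2/3 vs 1 (assumed) | R² | SE inflation | SE with grade | Power with grade |
|---|---|---|---|---|
| 5 mm | 1.1% | 0.6% | 3.066 | 90.3% |
| 10 mm | 4.4% | 2.3% | 3.014 | 91.3% |
| 15 mm | 10.0% | 5.4% | 2.926 | 92.8% |

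**4. Simulation of the design**

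4,000 trials per setting: 260 participants, 65 per site, blocks of 4 within site by grade, 10% loss, assumed site SD 5 mm, and a single week-24 change score. Both columns of each pair use a random site intercept, as planned.

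| Gap | Model SE, no grade / grade | Power, no grade / grade | Type I error, no grade / grade |
|---|---|---|---|
| 5 mm | 3.012 / 2.995 | 91.6% / 91.7% | 5.1% / 5.2% |
| 10 mm | 3.011 / 2.942 | 91.3% / 91.9% | 4.5% / 5.0% |
| 15 mm | 3.010 / 2.848 | 92.4% / 94.0% | 3.8% / 5.1% |

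The Monte Carlo standard error of a 5% rate is √(0.05 × 0.95/4000) = 0.34 points, so only the 15 mm row is clearly below nominal.

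At 15 mm the estimate's actual standard error was 2.85 without grade and 2.83 with it. The balance is therefore already in the estimate; it is the reported standard error of 3.01 that is too large. For the same reason the simulated power gains (0.1, 0.6 and 1.6 points) are smaller than those implied in step 3.

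**5. Random versus fixed site (gap 10 mm, site SD 5 mm)**

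| Model | Model SE | Power |
|---|---|---|
| Random site | 3.011 | 91.3% |
| Fixed site | 3.014 | 91.3% |
| Random site + grade | 2.942 | 91.9% |
| Fixed site + grade | 2.944 | 91.9% |

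The form of the site term makes no practical difference, because treatment is balanced within site.

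**The case against.** The best case for leaving the model alone has four parts.

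- **Grade may not be prognostic here.** The cited dose-response evidence is from population-based studies. This trial excludes Grade 0, requires at least 40 mm of pain, collapses grade to two levels and adjusts change for baseline pain. An expected difference in treatment effect by grade does not make grade prognostic. This stands: the size of the effect is unknown and could be near zero.
- **Grade is used elsewhere.** It defines a pre-specified subgroup analysis, and it could enter through the missing-data sentence. Neither commits the primary model to it.
- **An article condenses.** Silence would be no finding. But the article lists the covariates of both models, and its amendments table shows that covariate adjustment was deliberately revised in version 1.6.
- **The gain is small and the error is safe.** This stands.

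A reader might infer more than the documents support:

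- *That the precision from stratification is lost.* It is not. Site is in the model, and the balance on grade remains in the point estimate.
- *That a random intercept with only four sites drops site and costs power.* Four sites do estimate a between-site variance poorly. But an estimate near zero arises when the observed site differences are about the size of sampling noise, so little is at stake, and step 5 shows no gain from fixed effects.
- *That the trial is underpowered.* The 90% was computed without credit for stratification and is met without grade.

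**Conclusion.** The point holds for grade only. The stated primary and additionally adjusted pain models omit a stratification factor, so if grade predicts pain change the analysis is mildly conservative. With grade explaining 1.1% to 10% of the variance of pain change, the standard error is inflated by about 0.6% to 5.4%. Power at 10 mm goes from 90.0% to between 90.3% and 92.8% once grade is added, and by simulation the gain is nearer 0.1 to 1.6 points. Validity is not threatened and there is no shortfall against the planned 90%.

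The omission itself is certain from the text; its size is not. The grade gaps and site SD are assumptions. The variance share is taken against the unadjusted SD of change, whereas the model also adjusts for baseline pain, and the simulation left out baseline pain and the repeated measures. This is a small improvement worth making because it is nearly free, not a flaw that undermines the trial.

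**What to change.** Add effusion-synovitis grade as recorded at randomisation (1 versus 2/3) as a fixed covariate in the primary pain model and in the additionally adjusted pain model, and specify this before unblinding. It costs one line of text and one degree of freedom, and the variable is already held for every randomised participant.

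Site may stay as a random intercept. Fixed site effects are a reasonable choice with four sites, but should not be presented as a gain in precision. The effusion-synovitis models need no change: they already adjust for the baseline value of that outcome, and the two-level grade would add little to it.

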### Sample size calculations

#### Pain (primary outcome)

Based on in-house data from the 4Jointz trial [45], 234 participants will give us 90% power, with 5% probability of type 1 error (alpha=0.05) to detect a 10mm difference between diacerein and placebo on the VAS pain scale (standard deviation (SD) of pain change 25.5 in the placebo group and 21.5 in drug group). To allow for a 10% loss to follow-up, we need 260 participants (130 in each arm). We expect to see a larger effect than published in the diacerein meta-analysis (8.7mm) [20] due to targeting the therapy for those with effusion-synovitis. We will have >99% power to detect a difference of 15 mm, the minimum clinically important difference (MCID), on a 100mm VAS for OA trials [39].

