The steering committee recommended that a doubling of serious adverse events (SAE) in one group compared to the other will trigger a safety review by the Data and Safety Monitoring Board (DSMB). If a safety review is triggered, the DSMB will review the unblinded data, and make recommendations about stopping the trial. A death (or other significant SAE) in the drug group may lead to stopping the study. When the DSMB reviews the unblinded data, they will make a judgement about whether the death/SAE is clearly attributable to the drug, and this will inform the decision about stopping the trial. No interim analyses will be conducted for efficacy. As this is a trial for OA (a non-life-threating condition), no level of efficacy would outweigh SAE concerns. An extraordinary meeting of the DSMB may be called by the Steering Committee at any time if there is concern about the number or severity of AEs.

Based on our hypothesis that diacerein will be more effective in participants with moderate to severe effusion-synovitis, we will perform a stratified analysis based on the size of effusion-synovitis at baseline (mL), and ordinal effusion-synovitis score (Grade 1 or 2/3) at baseline. Other pre-specified stratification analyses will be performed to examine which subgroups may respond better to treatment based on these variables: radiographic knee OA severity, degree of neuropathic pain, depression, fibromyalgia-ness, and co-pathology present on MRI. Statistical significance will be set as a two-sided *P* value <0.05.

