Statistical analysis	1. If there are baseline imbalances between treatment groups, we will consider adjusting for them based on whether we regard the imbalance as clinically significant. 2. Per protocol analyses will be performed as the secondary analyses, for study participants consuming ≥80% of capsules.	1. We will adjust for the baseline values of the corresponding outcome measure (e.g. change in pain scores will be adjusted for baseline pain scores). We will also run a model that additionally adjusts the primary outcome for sex, analgesic medication, and depression. 2. Per protocol analyses will be performed as the secondary analyses, for study participants consuming ≥80% of study medication between baseline and week 24 (allowing for 1 capsule (50 mg) per day).	For item 1, the trial statistician, along with the data safety monitoring board and steering committee recommended some minor changes to the statistical analysis plan, to adhere to best practice in RCT analysis. For item 2, this is an update to reflect the change in dose of intervention (see above).

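### The primary model's missing-data covariates are left open, and no stated analysis tests departure from missing at random

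*Protocol article*

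**What the plan says.** The primary analysis is a linear mixed-effects model for change in VAS pain. It has treatment, month and their interaction, random intercepts for centre and participant, and adjustment for the baseline value of the outcome. A further model of the primary outcome adds sex, analgesic medication and depression.

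The Statistical analysis section describes two ways of dealing with missing data:

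- In the regression models, loss to follow-up and nonresponse will be "addressed by adding baseline complete variables that can explain the missingness to the regression models". The variables are not listed, and no rule or time point for choosing them is given.
- "Secondary analysis for missing data will be performed using multiple imputation by chained equations", with 20 imputations run by treatment group from complete baseline variables and the observed outcomes. This analysis is stated to assume missing at random.

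Table 3 (Protocol amendments) records the current rule on covariate adjustment: "We will adjust for the baseline values of the corresponding outcome measure". It replaced adjustment that depended on observed baseline imbalance, and the stated reason was best practice in the analysis of randomised trials.

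The Withdrawal section adds that participants who stop treatment will be asked whether they are willing to complete the remaining assessments.

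**The concern.** There are two linked weaknesses.

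First, the rule for the primary model is open. Whether a baseline variable is complete, and whether it explains missingness, would ordinarily be judged from trial data. Elsewhere in the same section the authors name covariates when they mean to fix them, so the unnamed set stands out. A primary estimate whose covariates can be settled late leaves room for choice that the amendment on baseline adjustment otherwise reduced.

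Second, the secondary analysis does not relax the assumption of the first. The article attaches missing at random only to the imputation, but a likelihood-based mixed model with covariates added to explain missingness rests on the same assumption. If participants lost from the diacerein arm had worse pain than their earlier scores predict, both analyses would tend to miss it.

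Unequal loss is plausible here. The Background names diarrhoea as the most notable adverse event of the drug, and Table 3 reports that side effects kept some participants in this trial from increasing their dose at week 2. At stake are the size of the primary effect and how well its robustness can be shown.

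**Working it through.** **Inputs from the Sample size calculations and Statistical analysis sections.** SD of pain change 25.5 (placebo) and 21.5 (diacerein); target difference 10 mm; power 90%; alpha 0.05, with a two-sided test ("Statistical significance will be set as a two-sided" P value below 0.05); 10% loss; 260 randomised, 130 per arm.

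**The plan's own figure.** It states that "234 participants will give us 90% power". With the normal approximation:

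- n per arm = (1.960 + 1.282)² × (25.5² + 21.5²) / 10² = 10.51 × 1112.5 / 100 = 116.9, so 117 per arm and 234 in total.
- 234 / 0.90 = 260.

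Both figures reproduce.

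**Precision at 117 per arm.**

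- SE = √(1112.5 / 117) = 3.08 mm.
- Smallest significant difference = 1.96 × 3.08 = 6.04 mm.

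**Bias if missing at random fails.** Let p be the proportion missing at week 24 in an arm, and δ the amount by which the missing outcomes are worse than the model predicts. Then

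overstatement of benefit = p(diacerein) × δ(diacerein) − p(placebo) × δ(placebo).

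The splits below keep overall loss at the planned 10%, with the same δ in both arms. Splits and δ are assumptions; the documents give neither.

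| Loss, diacerein / placebo | δ = 10 mm | δ = 20 mm |
|---|---|---|
| 15% / 5% | 1.0 mm | 2.0 mm |
| 12% / 8% | 0.4 mm | 0.8 mm |
| 10% / 10% | 0 | 0 |

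Relative to the SE, the non-zero values run from 0.4 / 3.08 = 0.13 to 2.0 / 3.08 = 0.65.

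**Shift needed to lose significance.** If only the diacerein arm is shifted and the SE is held at 3.08 mm, the tipping δ is (observed effect − 6.04) / p(diacerein). The 8.7 mm row uses the meta-analysis effect quoted in the sample-size section.

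| Observed effect | 10% missing on diacerein | 15% | 20% (all 26 planned losses) |
|---|---|---|---|
| 10 mm | 39.6 mm | 26.4 mm | 19.8 mm |
| 8.7 mm | 26.6 mm | 17.7 mm | 13.3 mm |

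A 10 mm result would therefore be hard to overturn at the planned loss. A result nearer 6 mm, or loss concentrated in the diacerein arm, would be more exposed. A sensitivity grid that stopped at 20 mm would not reach the tipping point for a 10 mm effect with 15% loss on diacerein.

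**The case against.** The strongest reply is about scope. Auxiliary-variable lists and analyses under missing not at random are usual content of a statistical analysis plan, and that plan is not shown. It may name the variables and add such an analysis. This has force against a complaint of bare absence. It has less force here, because the article does state its missing-data methods: one is an open rule inside the primary model, and both rest on the same assumption.

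The design also limits the risk. Follow-up is offered after treatment stops, and unblinded participants stay in follow-up. Contact can be by telephone, email or Telehealth. VAS is collected at weeks 4, 8, 12, 16 and 20, so the models condition on pain observed before loss. Nothing in the documents shows that participants who leave because of diarrhoea have unexpectedly bad knee pain. All of this stands, and it is why the point is moderate.

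A reader might be tempted by three stronger claims, which the documents do not support:

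- *The two analyses will agree whatever the truth.* The imputation is run by arm and is not said to use the same variables as the mixed model, so the results may differ. What can be said is that agreement would be no evidence for missing at random.
- *The covariates can only come from the trial data.* Likely predictors of loss could be named in advance or chosen blind to allocation. The article simply does not commit to either.
- *Late covariate choice would move the estimate by about 1 mm by chance.* That figure, 3.08 × √0.1, needs the added variables to explain a further 10% of outcome variance. They would be selected for predicting missingness, so this R² is unsupported. Adjustment for baseline covariates does not in itself bias a randomised comparison.

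The parallel with the amendment is also loose, since that change concerned baseline imbalance and not missingness.

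**Conclusion.** The point holds in a limited form. The stated rule leaves the covariates of the primary model open to choice after data are seen, and neither stated missing-data analysis probes departure from missing at random.

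The consequence is likely to be modest: about 0.4 to 2.0 mm of overstated benefit, or 4% to 20% of the 10 mm target. This rests on assumed loss splits of 12%/8% to 15%/5% and on missing outcomes 10 to 20 mm worse than predicted in both arms. The bias disappears if loss and departure are the same in both arms. The documents do not show that unequal loss or such a departure will occur, only that side effects make unequal loss plausible. The sample size is unaffected. The change is worth making because it is cheap and concerns the primary analysis.

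**What to change.** - Replace the rule of adding variables that explain missingness with a primary covariate set fixed before unblinding: baseline VAS, site, and effusion-synovitis grade (1 or 2/3). Grade is a stratification factor under Randomisation and blinding, but the stated primary model omits it. Baseline VAS and centre are already in the model.
- Use predictors of missingness only as auxiliary variables in the planned imputation.
- Add a delta-adjusted version of that imputation. Shift imputed week-24 VAS towards worse pain, first in the diacerein arm alone and then in both arms, and extend the range until significance is lost. Where equal shifts meet equal loss the estimate does not move, so in that case report the result up to the limit of the scale.

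The cost is a change of wording and a few extra runs of an imputation already planned. Recruitment was still open when the article was submitted and no interim efficacy analysis is planned, so the change could be made without knowledge of results.

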### Objective

We are conducting a multi-centre, randomised, double-blind, placebo-controlled trial aiming to compare the effect of diacerein vs. placebo on knee pain and effusion-synovitis over 24 weeks in 260 knee OA patients with effusion-synovitis. We hypothesise that diacerein will improve knee pain over 24 weeks (primary hypothesis) and decrease effusion-synovitis over 24 weeks (secondary hypothesis) compared with placebo. We also hypothesise that diacerein will be more effective in patients with moderate to severe effusion-synovitis (secondary hypothesis).

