##### Pre-specified stratification analysis based on size of effusion-synovitis (secondary analysis)

One hundred twenty-two participants at the end of the trial with Grade 2 or 3 effusion-synovitis will give us 80% power, and 5% probability of type 1 error (alpha=0.05) to detect a 12mm difference between diacerein and placebo on the VAS pain scale (SD of pain change 25.5 in the placebo group and 21.5 in drug group) in this participant sub-group. Based on the distribution of effusion-synovitis in our vitamin D trial for knee OA [55], we expect to recruit approximately 145 participants with either Grade 2 or 3 synovitis.

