## Discussion

We propose a multi-centre, randomised, double-blind, placebo-controlled trial to determine the effect of diacerein on knee pain and effusion-synovitis over 24 weeks in patients with clinical knee OA, significant knee pain, and effusion-synovitis. If diacerein proves effective in patients with moderate to severe effusion-synovitis, it will offer an important therapeutic approach for this inflammatory phenotype of knee OA.

Diacerein is an anti-inflammatory drug that blocks IL-1β, a key marker of inflammatory OA. IL-1 presents in OA joint tissues and plays a key role in synovitis, and the expression of IL-1 is associated with more severe pain and rapid progression of OA. The findings of previous studies suggest that diacerein had a beneficial effect on both knee pain and JSN assessed by x-ray [20]. Considering the mechanism of action of diacerein, it is likely that diacerein has a stronger effect on pain and structural progression in patients with joint inflammation, as indicated by MRI-detected effusion-synovitis. Moreover, by quantitative and semi-quantitative evaluation of effusion-synovitis, this study will determine whether diacerein performs better in patients with more effusion-synovitis, which may reflect a greater component of pain being explained by joint inflammation.

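### The secondary hypothesis compares treatment effects between effusion-synovitis strata, but the named analysis and the 80% power address only the effect within a stratum

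*Protocol article*

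**What the plan says.** All references are to the protocol article.

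- **Objective:** "We also hypothesise that diacerein will be more effective in patients with moderate to severe effusion-synovitis (secondary hypothesis".
- **Statistical analysis:** citing that hypothesis as its basis, the plan says "we will perform a stratified analysis based on the size of effusion-synovitis at baseline (mL), and ordinal effusion-synovitis score", the score being split as Grade 1 or 2/3. Five further variables are to be stratified in the same way: radiographic severity, neuropathic pain, depression, fibromyalgia-ness and MRI co-pathology. The threshold is "Statistical significance will be set as a two-sided *P* value <0.05". The only interaction named in the mixed model is treatment by month.
- **Sample size calculations, stratification analysis:** 122 Grade 2/3 completers "will give us 80% power, and 5% probability of type 1 error (alpha=0.05) to detect a 12mm difference between diacerein and placebo". The text places this contrast within that sub-group and expects about 145 such participants to be recruited.
- **Randomisation and blinding:** grade (1 or 2/3) is a randomisation stratum.
- **Discussion:** "this study will determine whether diacerein performs better in patients with more effusion-synovitis".

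**The concern.** Whether the drug is more effective in one stratum than in the other is a question about the difference between two treatment effects. A drug-placebo contrast inside Grade 2/3 estimates only one of them. Finding significance in Grade 2/3 but not in Grade 1 does not show that the effects differ, because the two results can fall on either side of 0.05 when the underlying effects are equal.

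The phenotype message of the trial rests on this hypothesis, and the Discussion promises an answer to it. A reader who takes the 80% as the power behind that promise would be misled about what 260 patients can show.

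**Working it through.** **Inputs (Sample size calculations).** SD of pain change 25.5 (placebo) and 21.5 (drug); 234 completers of 260, that is 10% loss; 12 mm in Grade 2/3; 10 mm overall; 8.7 mm from the cited meta-analysis; about 145 of 260 in Grade 2/3. Two-sided alpha 0.05; normal approximation.

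**1. The plan's own figures.** The sum of the variances is 25.5² + 21.5² = 1112.5.
- 12 mm at 80% power: n per arm = 1112.5 × (1.960 + 0.842)² / 12² = 60.6, so 61 per arm and 122 in all. This matches.
- 10 mm at 90% power: n per arm = 1112.5 × (1.960 + 1.282)² / 10² = 116.9, so 117 per arm and 234 in all; 234 / 0.9 = 260. This matches.

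**2. Standard error of the between-stratum difference.** Assume 10% loss and 1:1 allocation in each stratum.
- Grade 2/3: 145 × 0.9 = 130.5 completers, 65.25 per arm; SE = √(1112.5 / 65.25) = 4.13 mm.
- Grade 1: 234 − 130.5 = 103.5 completers, 51.75 per arm; SE = √(1112.5 / 51.75) = 4.64 mm.
- Interaction: √(4.13² + 4.64²) = 6.21 mm.

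**3. Power for the comparative hypothesis.**
- Difference detectable with 80% power: 2.802 × 6.21 = 17.4 mm. For scale, the plan's MCID for the treatment effect itself is 15 mm.
- 12 versus 0 mm: 12 / 6.21 = 1.93, giving about 49%. To reach 80% here would take about 492 completers (492 / 0.9, or 547 recruited).
- 12 mm in Grade 2/3 with 10 mm overall: the Grade 1 effect is (234 × 10 − 130.5 × 12) / 103.5 = 7.48 mm, a difference of 4.52 mm. Then 4.52 / 6.21 = 0.73, giving about 11%.

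**4. Chance that only Grade 2/3 is significant when the true effect is the same in both strata.**

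| Common effect | Power, Grade 2/3 | Power, Grade 1 | Only Grade 2/3 significant |
|---|---|---|---|
| 8.7 mm | 0.558 | 0.467 | 0.558 × (1 − 0.467) = 0.30 |
| 10 mm | 0.678 | 0.578 | 0.678 × (1 − 0.578) = 0.29 |
| 12 mm | 0.828 | 0.735 | 0.828 × (1 − 0.735) = 0.22 |

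**5. Sensitivity.** With exactly 122 Grade 2/3 completers and 112 in Grade 1, the interaction SE is 6.17 mm, the detectable difference is 17.3 mm, and the last column becomes 27%, 25% and 19%. The conclusion does not depend on the split.

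**The case against.** The best defence is that the article is condensed. It names no interaction test, but it does not exclude one, and the model for subgroups may be set out in an analysis plan that is not shown. A reader might infer that separate p-values within strata will decide the hypothesis; the text gives no such decision rule. This defence stands as far as it goes. It does not cover the mismatch: the article does fix an analysis type, a subgroup size and a power in answer to a comparative hypothesis, and all three concern the effect within a stratum. An interaction test specified elsewhere would not turn the 80% into power for that hypothesis.

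Other strong readings are tempting and should be resisted.
- *The 80% is mislabelled.* It is not. The sample size section confines it to the sub-group, and the figure reproduces. What is absent is any statement of power for the comparison.
- *A false subgroup conclusion is probable.* In the hypothesised direction the chance is 22 to 30%, and a false conclusion follows only if the pattern is then read as effect modification. Adding the trials in which only Grade 1 is significant (about 19% at a common 10 mm) would inflate the figure with results that contradict the hypothesis.
- *Error accumulates over all modifiers as if the tests were independent.* They cannot be independent, since every modifier divides the same patients again.
- *Baseline volume will be dichotomised.* No cut-point is stated, so none can be criticised.

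Finally, the powers above use unadjusted change SDs, whereas the plan adjusts for baseline and uses repeated measures. That would raise them somewhat.

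**Conclusion.** The point holds as a mismatch between question and method. The secondary hypothesis is comparative; the analysis named for it is stratified; the stated power belongs to drug versus placebo in Grade 2/3. Power for the comparison itself is low: about 49% in the extreme case of 12 versus 0 mm and about 11% for the difference implied by the plan's own effect sizes. With equal effects of 8.7 to 12 mm, a pattern that resembles confirmation appears in about 22 to 30% of trials.

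These figures assume equal SDs in the two strata, 10% loss in each, 1:1 allocation within strata, and no gain in precision from covariates or repeated measures. The primary outcome, its analysis and the overall sample size are not affected. This should be corrected, but it does not threaten the main result.

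**What to change.** - State that the secondary hypothesis is assessed by the treatment by grade (1 versus 2/3) interaction at week 24 in the full-sample model, with treatment by continuous baseline volume as a companion analysis.
- Report both interaction estimates with confidence intervals.
- Present within-stratum effects as descriptive and the five other modifiers as exploratory.
- Add to the sample size section that the 80% does not apply to the comparison between strata, which has low power: about 17 mm is needed for 80% under the plan's unadjusted SDs.
- Word the promise in the Discussion accordingly.

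The cost is wording only. Grade is already a randomisation stratum, and no further patients or data are needed. The drawback is that the subgroup claim becomes harder to make. The change should be made before unblinding, so that the choice of method cannot appear to follow the results.
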